## VII. TREATMENTS STUDIED

### ❖ JUSVINZA®

It is a sterile lyophilized powder containing 2.5 mg or 1.25 mg, in 2R glass flasks.

Active ingredients: Immunomodulator CIGB-258 peptide, obtained by chemical synthesis at the Center for Genetic Engineering and Biotechnology (CIGB, Havana, Cuba).

The composition of each vial is shown in the following table:

| Component               | Amount             | Function                      | Quality Standard                                        |
|-------------------------|--------------------|-------------------------------|---------------------------------------------------------|
| CIGB-258 peptide        | 2.5 mg o
1.25mg | Immunomodulator               | NP 4380C Injectable
according to the
manufacturer |
| Sucrose                 | 20.0 mg            | Stabilizer                    | NP 252 / USP                                            |
| Acetic acid 50 mM. pH 4 | 3.0 mg             | Acid, constituting the buffer | NP 020 / USP                                            |

**Action:** anti-inflammatory and immunomodulator effect.

## VIII. EVALUATION VARIABLES

### 8.1. Protocol variables

#### 8.1.1. Main variables

#### ❖ Evaluation of the anti-inflammatory effect:

Approved by:

[name] [name]

Signature:

[figure not shown]

Cargo:

Director of Biomedical Research, CIGB

Date:

13/05/2021

- ✓ We will calculate the percentage of high-risk patients recovering after a seven-day treatment with Jusvinza.
- ✓ We will calculate the percentage of severely ill patients recovering after a ten-day treatment with Jusvinza.
- ✓ We will calculate the percentage of critically ill patients recovering after a fifteen-day treatment with Jusvinza.

### 8.1.2. Secondary variables

1. Describe the clinical evolution of the patients.
2. Describe of the radiological evolution of the patients.
3. Quantify the inflammatory biomarkers in the serum (NLR, C-reactive protein, erythrocyte sedimentation, Ferritin, LDH, dimer-D, CPK, ASAT, ALAT).
4. Quantify the cytokines: IL-6, TNF $\alpha$  e IL-10.
5. Quantify the percentage of lymphocytes CD4, CD8 and Treg.
6. Describe the adverse events.

### 8.1.3. Control variables

Because of their possible effect on the therapeutic response, we will consider the following:

- a. Adherence of the patient to the treatment.
- b. Personal pathological history.
- c. Age (years)
- d. Sex (male / female).
- e. Skin color (white, non-white).
- f. Symptomatology (symptomatic, asymptomatic, pre-symptomatic)
- g. Time taken between the positive diagnosis of SARS-CoV-2 and the start of the first symptoms or contact.
- h. Previous treatments and those concomitant with the research product (anti-viral drugs, basic diseases)

---

Approved by:

[name] [name]

Signature:

[figure not shown]

Cargo:

Director of Biomedical Research, CIGB

Date:

13/05/2021

- i. Body mass index.
- j. Toxic habits (smoking, alcohol consumption).

## 8.2. Criteria for the success or failure of the individual, and of the therapy

- ☐ We will consider an **individual success** if the patient recovers; if there are no severe adverse events with a demonstrated causality.
- ☐ We will consider a **therapeutic success** if the hypothesis is demonstrated, in which 90% of the high-risk patients treated with Jusvinza do not reach the severe phases of the disease and then recover.
- ☐ We will consider an **individual failure** when a patient progresses toward a more severe condition or death and if there is a definitive interruption of the treatment due to the presence of severe adverse events, with a causal relationship attributable to the product under study.
- ☐ We will consider a **therapeutic failure** when patients progress towards the more severe stages of the disease.

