### 3.3 Hypothesis

On considering that with the extensive study of the use of Jusvinza in Cuba, 85 % of the severe patients recovered, we expect that 90% of the high-risk patients treated with Jusvinza will not progress to the severe conditions of the disease and will recover.

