## V. GENERAL CONCEPT

### 5.1 Design of the trial

A retrospective, observational, monocentric study will be carried out with the primary aim of evaluating the effect of Jusvinza in the reduction of inflammation and the safety of its intravenous administration.

All patients with available information that have been treated with Jusvinza, according to the action protocol, between March 21 and July 29 of 2021, will be included.

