## XI. STATISTICS

### 11.1 Number of patients planned

We consider as the number of patients, all those having information according to this study, at the [name] Díaz Soto Hospital and complying with the inclusion criteria.

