### 11.2 Plan for the statistical analysis

#### 11.2.1 Set of data analyzed

There are two groups:

***“Treated with Jusvinza”***: defined as the patients that have been treated with Jusvinza, according to the the information in their clinical records.

***“Not treated with Jusvinza”***: defined as the patients that do not have any information in their clinical records of having been treated with Jusvinza.

.

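### Section 8.2 lets a raw 90% in high-risk patients count as the hypothesis demonstrated, with no allowance for sampling error and no set number of patients

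*Protocol*

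**What the plan says.** Protocol section 3.3 states the hypothesis as an expectation: "we expect that 90% of the high-risk patients treated with Jusvinza will not progress to the severe conditions of the disease and will recover". The figure offered in support concerns a different group, since it reports that "85 % of the severe patients recovered".

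Section 8.2 turns the expectation into a verdict on the drug. Therapeutic success is declared "if the hypothesis is demonstrated, in which 90% of the high-risk patients treated with Jusvinza do not reach the severe phases of the disease"; these patients must also recover. The matching failure criterion has no threshold: the therapy fails "when patients progress towards the more severe stages of the disease".

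The only estimation step for this group is in section 8.1.1: "We will calculate the percentage of high-risk patients recovering after a seven-day treatment with Jusvinza". Section 11.1 sets no target number: "We consider as the number of patients, all those having information according to this study". Section 5.1 takes all patients with available information who were treated "between March 21 and July 29 of 2021, will be included". Section 11.2.1 names two groups, the treated one being "defined as the patients that have been treated with Jusvinza, according to the the information in their clinical records". The protocol states no confidence level, test, error rate or minimum acceptable rate for high-risk patients.

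**The concern.** Read together, sections 8.1.1, 8.2 and 11.1 give this rule: divide the high-risk patients who did not progress and who recovered by all treated high-risk patients, and declare success if the result is at least 90%. A sample percentage at that level is compatible with a range of true rates, and the range is wide when the group is small. Calling the hypothesis demonstrated at that point claims a certainty the rule does not provide.

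The number of patients is also unknown in advance, so the strength of the verdict is unknown too. The same sentence is lenient with 20 records and fairly strict with 200. This matters beyond the hospital because section 14.1.1(e) sends the results to the regulator for the product's registration dossier.

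**Working it through.** **Inputs.** The threshold is 90% (section 8.2) and the expected rate is 90% (section 3.3). The number of high-risk patients, n, is not given, so I assume values from 10 to 500. The protocol has no sample size, power or error rate to reproduce. True rates of 80%, 85% and 88% are my illustrations, because the protocol gives no reference rate for high-risk patients.

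**Step 1: the rule as a formula.** Let X be the number of high-risk patients who do not progress and who recover, with X ~ Binomial(n, p) and patients taken as independent. Success means X ≥ c, where c is 0.9n rounded up.

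**Step 2: what a result just meeting the rule shows.** The exact (Clopper-Pearson) two-sided 95% interval for x out of n runs from the 0.025 quantile of Beta(x, n − x + 1) to the 0.975 quantile of Beta(x + 1, n − x).

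**Step 3: how often the rule declares success.** This is P(X ≥ c) at a given true p.

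| n | c | Exact 95% interval at c/n | p = 80% | p = 85% | p = 88% | p = 90% |
|---|---|---|---|---|---|---|
| 20 | 18 | 68.3% to 98.8% | 0.206 | 0.405 | 0.563 | 0.677 |
| 50 | 45 | 78.2% to 96.7% | 0.048 | 0.219 | 0.435 | 0.616 |
| 100 | 90 | 82.4% to 95.1% | 0.006 | 0.099 | 0.334 | 0.583 |
| 200 | 180 | 85.0% to 93.8% | 0.000 | 0.025 | 0.227 | 0.559 |

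**Step 4: behaviour at a true 90% over all n.** The round values in the table are favourable cases, because 0.9n is then a whole number. Over every n from 10 to 500 the probability runs from 0.42 (n = 19) to 0.74 (n = 10). It is above one half for about 70% of these n. It is below one half whenever n ends in 7, 8 or 9 (for example 0.464 at n = 99). If success needed strictly more than 90%, it would be 0.392, 0.431, 0.451, 0.466 and 0.478 at n = 20, 50, 100, 200 and 500.

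**Step 5: what a confidence-limit rule would require.** Suppose the lower 95% limit had to reach 90%.

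| n | Minimum successes | P(success), p = 90% | P(success), p = 95% |
|---|---|---|---|
| 50 | 50 | 0.005 | 0.077 |
| 100 | 96 | 0.024 | 0.436 |
| 200 | 189 | 0.017 | 0.700 |
| 500 | 464 | 0.019 | 0.988 |

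When all n patients succeed, the lower limit is 0.025^(1/n). This is just under 0.900 at n = 35 and 0.903 at n = 36, so the requirement cannot be met with 35 or fewer patients.

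With a minimum of 85%, taken purely as an example, the requirement is 93/100, 181/200 or 441/500. The chance of meeting it at a true 90% is then 0.21, 0.47 and 0.92.

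**The case against.** - **90% is the expected rate, not a null value to be beaten.** This stands. A reader might infer from the table that the rule gives a false positive more than half the time at 90%. The protocol does not support that. Success at a true 90% agrees with section 3.3, and Step 4 shows that *more than half* is not general. The argument rests on the intervals and on true rates below 90%.
- **The 85% scenario is not the protocol's.** This also stands. Its 85% concerns severe patients, so the figures illustrate the rule and do not describe an expected outcome. With 200 or more high-risk patients, success at a true 85% is already rare (2.5% or less).
- **Section 8.2 does not say how the hypothesis is to be judged demonstrated, and a statistical analysis plan could add an interval.** The raw-percentage reading is an inference, though it is the natural one. Leaving the interval method to that plan would be no fault. The success criterion itself is fixed in the protocol, however, and an interval reported elsewhere would not change what section 8.2 allows to be concluded.
- **Taking all available records is normal in a retrospective study and approaches a census.** This is correct, and the open number is not an error in itself. If the aim were only to describe these patients, sampling error would matter little. But section 4.2(c) looks to future patients and section 14.1.1(e) to registration, so the conclusion is meant to reach further.
- **The specific objectives are descriptive.** This is true of section 3.2, and it favours an estimate with its interval over a declaration of success.

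**Conclusion.** The point holds in a limited form. As written, section 8.2 can declare the hypothesis demonstrated on data compatible with true rates well below 90%. The lower limit is 68% with 18/20 and still 82% with 90/100. The weakness is material with tens of patients and modest with several hundred. The documents do not show which applies.

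This rests on three assumptions: the observed-percentage reading of section 8.2, independent patients, and assumed values of n.

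A reader might also infer that the lower confidence limit ought to reach 90%. The protocol does not support that either. It would replace an expected 90% with a rate shown to be at least 90%, and would fail about 98% of the time or more if the stated hypothesis were exactly true.

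**What to change.** In section 8.2:

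- Report the proportion of high-risk patients who do not progress and who recover with its exact two-sided 95% confidence interval. Do the same for the three main percentages in section 8.1.1.
- State that an observed 90% alone will be described as *consistent with the expected 90%*, not as the hypothesis demonstrated.
- Reserve *demonstrated* for a lower confidence limit that reaches a minimum rate for high-risk patients, stated and justified by the sponsor before analysis.
- If the sponsor chooses 90% as that minimum, say that it needs 96/100 or 189/200, cannot be met with 35 or fewer patients, and would succeed only about 0.5% to 2.4% of the time at the sizes checked if the true rate is exactly 90%.
- Give the therapeutic-failure criterion a threshold in the same edit. At present 90% success and failure could both be met by the same data.

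The cost is a few sentences and one interval per percentage, with no new data or patients. The conclusion will be more cautious and may be less favourable. The interval covers sampling error only and does not address confounding or the choice of comparator.

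### Section 8.2 can return therapeutic success and therapeutic failure on the same data, and its individual labels overlap or leave patients unlabelled depending on how an ambiguous *and if* is read

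*Protocol*

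**What the plan says.** Protocol section 8.2 states four rules.

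- **Therapeutic success** is declared "if the hypothesis is demonstrated, in which 90% of the high-risk patients treated with Jusvinza do not reach the severe phases of the disease"; the rule requires recovery as well. Section 3.3 gives the same target as an expectation: "we expect that 90% of the high-risk patients treated with Jusvinza will not progress to the severe conditions of the disease and will recover".
- **Therapeutic failure** is declared "when patients progress towards the more severe stages of the disease". The sentence gives no percentage and does not say which severity class it concerns.
- **Individual success** applies "if the patient recovers; if there are no severe adverse events with a demonstrated causality".
- **Individual failure** applies "when a patient progresses toward a more severe condition or death and if there is a definitive interruption of the treatment" because of severe adverse events "with a causal relationship attributable to the product under study".

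The protocol does not say which therapeutic rule prevails when both are met, and it does not explain the *and if*. Section 11.1 fixes no sample size: "We consider as the number of patients, all those having information according to this study".

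**The concern.** Success and failure rules should be exclusive, and exhaustive if every patient or study is to be labelled. These are neither.

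At the level of the therapy, the success rule tolerates up to 10% of high-risk patients falling short, while the failure rule, as worded, tolerates no progression. A result that supports the sponsor's hypothesis can therefore also meet the stated definition of failure.

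At the level of the patient, the meaning of the failure rule turns on one connective, and each reading leaves a different defect. A report that tabulates individual successes and failures could not classify every patient from the text alone.

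This matters because section 8.2 is where the protocol says how the result will be judged, and section 14.1.1 says the results go to the regulator for the product's registration dossier.

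**Working it through.** **1. Therapeutic rules.** The inputs are the 90% criterion and the failure sentence, both from section 8.2. There is no derived figure to reproduce, since 90% is a set target and no sample size, power or significance level is given.

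Among *n* high-risk treated patients, let *g* progress and let *r* neither progress nor recover. Read 90% as an observed share.

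- Success: (n − g − r)/n ≥ 0.90.
- Failure, as worded: progression occurs, so g ≥ 1 is enough.
- Both: g ≥ 1 and g + r ≤ 0.10n.

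Example with n = 100 and g = 5:

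- r = 0: 95/100 = 95%, so both verdicts apply.
- r = 5: 90/100 = 90%, so both still apply.
- r = 6: 89/100 = 89%, so only failure applies.

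The overlap thus needs both conditions: at least one progression, and at least 90% recovering unprogressed.

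**2. How likely the overlap is.** Assume r = 0 and a true progression probability *p*. Let X be the number who recover without progressing, X ~ Bin(n, 1 − p). Then

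P(both) = P(X ≥ 0.9n) − P(X = n), where P(X = n) = (1 − p)^n.

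For p = 0.05:

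| n (assumed) | P(X ≥ 0.9n) | 0.95^n | P(both) |
|---|---|---|---|
| 20 | 0.9245 | 0.3585 | 0.566 |
| 50 | 0.9622 | 0.0769 | 0.885 |
| 100 | 0.9885 | 0.0059 | 0.983 |

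Since p is also assumed, P(both) at other values is:

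| p (assumed) | n = 20 | n = 50 | n = 100 |
|---|---|---|---|
| 0.02 | 0.33 | 0.64 | 0.87 |
| 0.08 | 0.60 | 0.78 | 0.82 |

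**3. Individual rules.** Each type of patient is set against the text, with *and if* read first as a conjunction (both parts needed) and then as a list (*and also if*). Related means causally related to the product; a stop means a definitive stop for a severe related event.

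| Patient | Success? | Failure, conjunction? | Failure, list? | Problem |
|---|---|---|---|---|
| Recovers, no progression, no severe related event | yes | no | no | none |
| Progresses or dies, and is stopped | no | yes | yes | none |
| Dies of COVID-19, no stop | no | no | yes | no label under conjunction |
| Progresses, then recovers, no severe related event | yes | no | yes | both labels under list |
| Neither recovers nor progresses, no stop | no | no | no | no label under either |
| Recovers without progression, stopped | no | no | yes | no label under conjunction |
| Recovers without progression, severe related event, not stopped | no | no | no | no label under either |

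Neither reading gives exactly one label to every patient.

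**The case against.** **The failure sentence is only the loose complement of success.** This is probably what was meant, and reading it as more than 10% falling short would remove the clash. The text does not say so, however, and the sentence is not even confined to high-risk patients. The 90% target itself is stated consistently in the summary, section 3.3 and section 8.2, and the specific objectives are descriptive. So a reader who infers that the sponsor is free to choose any conclusion after seeing the data goes too far. What is unsettled is the failure verdict and its relation to success.

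**A reader might infer that every result from 90% to just under 100% meets both rules, or that 5% progression always does.** Neither holds. If 95% succeed and the other 5% neither progress nor recover, the high-risk group does not trigger failure. If 5% progress and more than a further 5% fail to recover, success is not met.

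**A reader might infer that the protocol says a COVID-19 death is not a failure.** That depends on taking *and if* as a conjunction. The document reads as a translation, and the repeated *if* can introduce a separate condition, in which case the death is a failure. Even under the conjunction this is a gap rather than a contradiction: a patient who died has not recovered, cannot be an individual success, and counts against the 90% criterion if in the high-risk group.

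**The main variables do not use these labels.** This stands. The recovery percentages by severity class in section 8.1.1 do not depend on either failure definition.

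**The sample sizes and the 5% are assumed.** This also stands. The probabilities show that the overlap would be common under plausible inputs; they are not predictions. They also take 90% as an observed share, although section 8.2 speaks of the hypothesis being demonstrated without defining that.

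**Conclusion.** The point holds in two parts.

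First, the therapeutic success and failure rules overlap whenever at least one high-risk patient progresses and at least 90% still recover without progressing. This follows from the wording and does not depend on the assumed numbers. Under 5% true progression, recovery of all others and 90% as an observed share, the double verdict has probability 0.885 at n = 50 and 0.983 at n = 100. Over the assumed range of 2% to 8% progression and 20 to 100 patients, it runs from 0.33 to 0.98.

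Second, the individual-failure sentence is ambiguous, and neither reading gives a complete and exclusive classification. The conjunction leaves some deaths unlabelled, the list reading labels some patients twice, and both leave unlabelled the patient who neither recovers nor progresses and is not stopped.

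The documents do not support the stronger claim that the main results are compromised. The defect is confined to the labels and verdicts of section 8.2.

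**What to change.** Amend section 8.2 as follows.

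1. **Therapeutic failure:** define it as the 90% high-risk criterion not being met, and delete the sentence without a threshold. The overlap is then zero for every n.
2. **Individual success:** keep the present condition (recovery, with no severe adverse event of demonstrated causality) and add that the patient did not progress to a more severe condition, which matches the 90% criterion. Keeping the adverse-event condition matters: if only definitive stopping were listed, a recovered patient with a severe related event who was not stopped would become a success, which section 8.2 now excludes.
3. **Individual failure:** replace *and if* by *or if*, and state that every patient who does not meet individual success is an individual failure. The listed reasons then serve as examples, and every patient has exactly one label.

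The cost is a few sentences and no new data. The addition in item 2 is a real choice, since a patient who progresses and later recovers becomes a failure; the sponsor should adopt it knowingly. Only the classification of outcomes changes. Patient care and the recovery percentages in section 8.1.1 stay as they are.

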## IX. ADVERSE EVENTS

### 9.1 Adverse reactions that may be observed and methods used to record them

The adverse events are classified according to type, duration, intensity, causality relationship, actions taken, and results, in the following gradesxviii:

- Grade 1 (*Mild*) Asymptomatic or symptoms of mild intensity. Only clinical observation or diagnostic observation are needed. Does not require treatment.
- Grade 2 (*Moderate*) Requires minimal intervention, i.e. local or non-invasive.
- Grade 3 (*Severe*) Not immediately life-threatening for the patient. Requiring hospitalization (or its prolongation). Disabling
- Grade 4 (*Severe*) Life-threatening for the patient. Requires urgent intervention.
- Grade 5 (*Severe*) Death related to the adverse event.

The analysis of the causality relationship between the adverse event and the drug under study will be carried out using the following qualitative analysesxix:

1. Definitive: An event that 1) shows a reasonable chronological relationship; 2) follows a known response to the drug under study; 3) there is no reasonable explanation that it may be produced by

Approved by:

[name] [name]

Signature:

[figure not shown]

Cargo:

Director of Biomedical Research, CIGB

Date:

13/05/2021

other factors such as the clinical condition of the individual or concomitant drugs administered; **4)** it disappears when its administration is stopped, and reappears when it is renewed.

2. Probable: An event that **1)** shows a reasonable chronological relationship after the administration of the drug; **2)** shows a known response pattern to the drug under study; **3)** there is no explanation due to other factors such as the clinical condition of the individual or concomitant drugs administered; **4)** it disappears when the administration is stopped, but it is not confirmed with its re-exposure.
3. Possible: An event that **1)** shows a reasonable chronological relationship; **2)** it may follow, or not, a known response pattern of the drug under study, but **3)** it may be produced by other factors such as the clinical condition of the individual or concomitant drugs administered.
4. Doubtful: the event is more probably related to other factors than to the drug involved.

No adverse events associated to the administration of Jusvinza by the intra-venous route have been described.

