|---------------------------------------|----------------------------------------------------------------------------------------------------------------------------------------------------------------------------------------------------------------------------------------------------------------------------------------------------------------|
| Design of the study                   | Retrospective, observational, monocentric study
We will collect the retrospective information of each patients using the clinical records as the source of primary information, as well as clinical laboratory results and radiologic imaging stored in the GALEN program of the participating institution. |
| Number of patients                    | We will include all positive patients to SARS-CoV-2 by RT-PCR with the available information, classified as of high-risk, severe and critical conditions, who were prescribed the use of Jusvinza.                                                                                                             |
| Frequency and duration of the therapy | According to the indications of the Action Protocol                                                                                                                                                                                                                                                            |
| Drug under study                      | Drug: Jusvinza (2.5 mg or 1.25 mg), intravenous administration.                                                                                                                                                                                                                                                |
| Safety evaluation                     | 

• Symptoms

• Vital signs

• Analytical results

• Imaging results

                                                                                                                                                                        |

---

Approved by:

[name] [name]

Signature:

[figure not shown]

Cargo:

Director of Biomedical Research, CIGB

Date:

13/05/2021

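### Section 9.1 makes a known response a condition for Definitive and Probable but supplies none, so a new, otherwise unexplained IV reaction fits no causality category

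*Protocol*

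**What the plan says.** Section 9.1 of the protocol sets out four causality categories.

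- **Definitive** has four conditions. The second is that the event "follows a known response to the drug under study". The fourth is that "it disappears when its administration is stopped, and reappears when it is renewed".
- **Probable** also has four conditions. The second is that the event "shows a known response pattern to the drug under study". Confirmation on re-exposure is not needed.
- **Possible** drops the need for a known pattern, but its third condition is that "it may be produced by other factors such as the clinical condition of the individual or concomitant drugs administered".
- **Doubtful** is for events more likely due to something other than the drug.

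The section then closes with "No adverse events associated to the administration of Jusvinza by the intra-venous route have been described". The Summary describes the product as "Drug: Jusvinza (2.5 mg or 1.25 mg), intravenous administration", and section 5.1 makes the safety of intravenous use part of the primary aim.

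Section 8.2 uses causality twice. Individual success requires recovery and applies "if there are no severe adverse events with a demonstrated causality". Individual failure uses a different term, a causal relationship *attributable* to the product. Neither term is linked to a category in 9.1.

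**The concern.** A causality scale that asks for a match with known reactions works when there is a reference list. Here the protocol gives no list, and for the route under study it says there is nothing to put on one. The list of terms nonetheless defines an unexpected adverse event and includes in it an event not seen before. The protocol thus foresees new reactions, but its scale has no place for the clearest kind: a well-timed event with no competing cause.

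Two things are at stake. The first is the safety condition in individual success. If it counts only the upper categories, a new severe reaction would not count against success. The second is the reported number of related severe events. Under section 14.1.1 the results go to the regulator for the product's registration dossier, and a low number could partly reflect the classification rule.

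**Working it through.** No figure is stated and none can be recomputed, so the check sets the rules side by side.

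**Inputs.** The category conditions and the IV statement come from 9.1, the route from the Summary, the success and failure criteria from 8.2, and the definition of an unexpected event from the list of terms. On earlier human experience, section 2.1 says only that the phase I trial in rheumatoid arthritis showed safety and that a good safety profile was seen in the 187-patient phase II trial. It names no reaction.

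**Test case.** Take a new event after IV dosing with reasonable timing, no other explanation, and resolution when administration stops, with no re-exposure.

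| Category | Timing | Known response | Other cause | Course | Fits? |
|---|---|---|---|---|---|
| Definitive | met | **not met** | met (none) | not met (no re-exposure) | no |
| Probable | met | **not met** | met (none) | met | no |
| Possible | met | not required | **not met** (a possible other cause is presumed) | no condition | no |
| Doubtful | no condition | no condition | **not met** (another cause must be more likely) | no condition | no |

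The event fits 0 of 4 categories. For Probable, the known-response condition is the only obstacle. Without it the event is Probable, and it would be Definitive if it also recurred on re-exposure. In a retrospective record review, information on re-exposure is available only by chance.

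**Consequence in 8.2.** The term used for success can be read in three ways.

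1. Definitive only: the test event does not count against success.
2. Definitive or Probable: it still does not count.
3. Possible or higher: it counts only if the rater puts it in Possible despite the third condition of that category. Events that do have another possible cause would count.

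Under readings 1 and 2 the safety condition has almost no force for new reactions.

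**What does not depend on the rating.** The main variables in 8.1.1 are percentages recovering. Therapeutic success in 8.2 is the 90% rule for high-risk patients. Adverse events are described without a causality filter (objective 4 in 3.2 and item 6 in 8.1.2), are classified in 9.1 by type, duration, intensity, action and result as well as causality, and are recorded on the form in 10.1.

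**The case against.** A reader might infer that no event of any kind can be rated Definitive or Probable, so that a finding of no related severe events is guaranteed in advance. The documents do not support that, for four reasons.

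- The scale refers to a known response to the drug, not to the IV route. The closing sentence of 9.1 covers IV use only, and the protocol never says that no reaction is known by other routes. The definition of an unexpected event also points to a researcher's handbook, if one exists, which could hold a reaction profile.
- It is tempting to add that COVID-19 always offers another explanation. The protocol does not say so. Definitive asks whether another explanation is reasonable, which is judged case by case, and the population includes moderately ill patients.
- The causality term in 8.2 is undefined. That the safety condition cannot fail is one reading of it, not a consequence of the text.
- A new severe event would still be recorded, graded and described, so it would not go unseen.

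All four stand, and they limit the point. They do not remove it. Knowledge from another route helps only if the new event resembles it, and the protocol gives the rater nothing to compare with. A reaction that really is new fails the known-response condition whatever document is consulted. The gap between Probable and Possible also remains.

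**Conclusion.** The point holds within limits. On the information in the protocol, a new IV event with plausible timing, no other explanation and resolution on stopping cannot be rated Definitive or Probable, and it fits neither lower category. That is a fault in a rule the protocol itself fixes.

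The effect is confined to individual success and failure and to any summary of related events. The main variables, the 90% rule and the description of adverse events are untouched. No numerical size can be given, because the protocol states no event rates.

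The conclusion rests on two assumptions: that no reaction profile exists in a document outside the protocol which would cover the event, and, for the effect on individual success, that the term in 8.2 means the upper categories. If Possible also counts, the safety condition can fail for events with another possible cause.

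**What to change.** 1. **Section 9.1.** State that the known-response condition is waived for events with no established IV profile. Such an event is then rated on timing, absence of another explanation, and course after stopping or re-exposure. The test case above becomes Probable.
2. **Section 8.2.** Use one causality term for both individual success and individual failure, and name the categories it covers. The choice of cut-off is the sponsor's. Setting it at Possible is a real trade-off, since in severe and critical COVID-19 it could bring in many events caused by the disease.
3. **Reporting.** Tabulate grade 3 or higher events by disease severity class, both with and without the causality filter. The unfiltered description is already planned; the paired table shows how much the filter removes.

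The cost is two wording changes and one table, from data already collected on the form in 10.1. The downside is that a few more events may be rated as related. The waiver does not help with a fatal event, which cannot meet the condition of disappearing on stopping, so the unfiltered table is needed as well.
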